### Inclusion criteria

Participants will be included if they meet the following criteria:
Meet the criteria of DSM-5™ and ICD-10 for mild-moderate depression;HAMD-17 ≤ 24 and ≥ 8;Suffering chronic musculoskeletal pain (location at the neck, back, and limb) more than 3 months and VAS score ≥ 4;Aged between 18 and 65;No acupuncture therapy during the past 3 months before enrollment; andVoluntarily participating in this trial with a written informed consent form.

### Exclusion criteria

Participants with the following conditions will be excluded:
Suicidal ideation or SCL-90 depression score > 26;Bipolar disorder or schizophrenia;Malignant pain caused by cancer pain syndrome;Suffering severe pain, VAS ≥7;Headache and visceral pain such as stomachache;Pregnant or breastfeeding women;Complications of severe systemic diseases such as diabetes mellitus, tumors, or others considered not suitable to participate in the trial; andHad acupuncture treatment in the last 3 months.

### Sample size calculation

In this study, a priori analysis was used to calculate the sample size. The HAMD-17 and BPI scores were used to calculate the sample size, and a larger sample was used. The HC participants did not have depression and pain symptoms, so the HC group will not be scored on HAMD-17 and BPI. Two group statistics were calculated for the sample size, and a *T* test was applied. According to the two-sample *T* test with *α* = 0.05, 32 depression comorbid CMSP participants were required to achieve 80% power. Allowing for a dropout of 15% at the end treatment time point, the recruitment goal of depression comorbid CMSP participants was 48 subjects (24 per group). The HC participant count was calculated to be 12, with a ratio of 2:2:1, as previously described. Therefore, a total of 60 participants will be recruited.

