## Discussion

Depression and CMSP commonly coexist, which makes clinical treatment very difficult [29]. Despite huge costs, current pharmacological and psychological interventions have limited acceptability and effectiveness. Thus, patients are keen to have a cost-effective treatment. According to the American College of Physicians, acupuncture increases the response to second-generation antidepressants [30]. Previous studies also showed that acupuncture has clinical efficacy on depression and related symptoms, such as insomnia [15, 17, 18]. A systematic review showed that acupuncture is a cost-effective treatment for chronic pain [31]. Whether acupuncture has clinical efficacy on combined depression and CMSP is uncertain. On this basis, we designed this study, which meets CONSORT guidelines [32]. This trial will provide evidence on the clinical efficacy of acupuncture as a potential treatment for comorbid depression and CMSP. In addition, we will explore the mechanism of acupuncture’s antidepressant and analgesic effects from an epigenetic perspective.

Even so, there are some limitations of this study. First, it is a single-blind study, which may cause partial bias in the results. We will try our best to overcome this bias by allocating the different groups in different places to receive treatment. Second, the adherence of participants may be poor because the treatment period lasts 8 weeks. The study size is calculated on the hypothesis of a 15% loss rate, but it will be necessary to ascertain that there is no bias between the two intervention groups. Third, in this study, we performed a 4-week follow-up, and long-term follow-up will be more credible. Finally, there will be a skewed sex ratio in this study, because in traditional Chinese culture, men are generally unwilling to seek help, especially for mental disease. This bias was also present in our previous study.

We have presented the design and protocol for the clinical efficacy of acupuncture on mild-moderate depression comorbid with CMSP. On completion, this study will validate the clinical efficacy of acupuncture and its underlying mechanism.

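### The step from 32 required patients to a target of 48 does not follow from the stated 15% dropout, which gives 38; the target errs on the safe side, but the derivation needs reconciling

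*Protocol article*

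**What the plan says.** The Sample size calculation section of the protocol article sizes the comparison of real with sham acupuncture on HAMD-17 and BPI, taking the larger of the two results. It gives the test and level ("According to the two-sample *T* test with *α* = 0.05") and the requirement ("32 depression comorbid CMSP participants were required to achieve 80% power"). It then makes dropout the reason for the larger target: "Allowing for a dropout of 15% at the end treatment time point, the recruitment goal of depression comorbid CMSP participants was 48 subjects", which is 24 per group. The healthy controls follow from the allocation ratio: "The HC participant count was calculated to be 12, with a ratio of 2:2:1, as previously described". The total is 60.

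The limitations paragraph of the Discussion repeats the allowance: "The study size is calculated on the hypothesis of a 15% loss rate". Neither place gives any other reason for moving from 32 to 48. The article does not state whether the test is one- or two-sided, nor the difference and SD behind the 32.

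**The concern.** The three figures are presented as one chain: 32 needed, 15% lost, so 48 recruited. An inflation for 15% loss adds about 6 patients to 32, and the article adds 16. The gap of 10 patients is too large for rounding. Because the Discussion repeats the 15%, a single slip in the sample size section is a less likely explanation.

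What is at stake is which evaluable number the 80% power belongs to. A reader who takes 32 at face value would conclude that the trial can lose a third of its 48 patients and still have its planned power. That is so only if 32 is the true requirement. If the calculation really asked for about 40, the same loss would leave the trial short.

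**Working it through.** **Inputs from the article.** Required evaluable patients 32 (16 per arm at 1:1), power 80%, alpha 0.05, two-sample t test, dropout 15%, target 48 (24 per arm).

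**Trying to reproduce 48.**

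- Standard inflation, n/(1 − d): 32/0.85 = 37.6, so 38. Per arm: 16/0.85 = 18.8, so 19, again 38 in total.
- Shortcut, n × (1 + d): 32 × 1.15 = 36.8, so 37.
- 32 read as a per-arm number: 32/0.85 = 37.6, so 38 per arm and 76 in total.
- Dropout applied twice: 32/0.85² = 44.3. Three times: 32/0.85³ = 52.1.
- A further 15% inflation for a non-parametric test: 32 × 1.15/0.85 = 43.3.

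None of these comes within 2 patients of 48. Doubling the dropout to 30% gives 32/0.70 = 45.7, so 46, but that contradicts the stated 15%.

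**Working back from 48.**

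- Loss implied by 32 and 48: 1 − 32/48 = 33.3%.
- Evaluable patients implied by 48 and 15%: 48 × 0.85 = 40.8.
- A requirement of 20 per arm would give 20/0.85 = 23.5, so 24 per arm, which is the stated target. The article mentions no requirement of 40.

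**Excess over the stated inputs.** 48 − 38 = 10 patients; 10/38 = 26%.

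**Power under each reading** (noncentral t, alpha 0.05; two-sided is an assumption, with one-sided results alongside). Here d is the standardised difference that the stated numbers imply. The article does not give it.

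| Reading | Implied d, two-sided (one-sided) | Evaluable per arm | Power, two-sided (one-sided) |
|---|---|---|---|
| 32 is right, no excess | 1.02 (0.90) | 16 | 80% (80%) |
| 32 is right, 38 analysed | 1.02 (0.90) | 19 | 87% (86%) |
| 32 is right, 48 recruited less 15% | 1.02 (0.90) | 20 to 20.4 | 88-89% (87-88%) |
| Requirement was 40, met | 0.91 (0.80) | 20 | 80% (80%) |
| Requirement was 40, only 32 complete | 0.91 (0.80) | 16 | 70% (72%) |

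**The case against.** The strongest reply is that nothing is lost. In the readings where 15% is the true allowance, 48 recruited patients deliver at least 80% power at 15% loss, and if the loss were 33%, 48 would still leave the 32. The Background calls the study a pilot. The analysis section specifies intention-to-treat with the latest assessment carried forward, so nominally all 24 per arm are analysed; at d = 1.02, two-sided, that is about 93% power, before any dilution from carried-forward values. Most of this stands, and it sets the weight of the point: a wrong derivation, not an inadequate target.

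A reader might go further and infer that 32, 15% and 48 cannot all be true. The documents do not support that. The three can coexist if a margin was added without being declared. What fails is the statement that the 15% allowance leads to 48.

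A reader might also infer that the 12 healthy controls and the total of 60 are wrong. They follow correctly from 48 under the 2:2:1 ratio and stand as long as 48 stands.

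Finally, because 40 fits 15% and 48 so neatly, it is tempting to declare 40 the intended figure, with d about 0.91. That is solved backwards from the target and has no support in the text. Nor does the missing effect size carry the point. A condensed article may leave it to the full protocol, and the arithmetic fails without it.

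**Conclusion.** The point holds as an error of derivation. With 32 required and 15% lost, the target is 38, and 48 is 10 patients (26%) higher for no stated reason. Either the 32, the 15% or the reason given for 48 is wrong, and the article does not settle which.

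The direction is conservative. If 32 is right, the design has about 88-89% power at 15% loss rather than the printed 80%. If the requirement was about 40, the target is right, the 32 is the error, and power with 32 completers is about 70%. These power figures assume a two-sided test, 1:1 allocation and analysis of completers; the one-sided figures differ by no more than about 2 percentage points. The mismatch between 32, 15% and 48 depends on none of these assumptions.

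**What to change.** Keep 48 patients, 12 healthy controls and 60 in total. Go back to the original calculation and restate the Sample size calculation section, and the matching sentence in the Discussion, so that evaluable number, dropout allowance, target and power agree.

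- If 32 and 15% are confirmed, say that they require 38, that 48 includes an extra margin, and that expected power at 15% loss is about 88-89% (if the test was two-sided).
- Otherwise correct the 32 or the 15% from the original inputs.

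In either case, give the HAMD-17 and BPI differences, the SDs and the sidedness actually used. Do not solve an effect size backwards from 48; that would put a post hoc assumption into the plan.

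The cost is a few sentences of wording. Recruitment, allocation and analysis do not change.

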### Recruitment of participants

This trial will take place at the outpatient department of acupuncture and moxibustion, Second Affiliated Hospital of Guangzhou University of Chinese Medicine, China. Outpatients will be recruited via posters in the hospital and via Internet advertisement.

### Blinding

The participants, outcome assessors, and statisticians will be blinded to treatment allocation. All participants will be informed that they have an equal opportunity for allocation to the RA group or SA group before enrollment. In addition, to reduce bias during the intervention period, participants will be treated separately to prevent communication. All treatment sessions will be performed by trained and experienced acupuncturists. The acupuncturist will not provide any clues about the allocation information to the participants, assessors, or statisticians.

### Patient and public involvement

Neither patients nor the public will be directly involved in the design of the study and/or involved in the conduct of the study. The intervention in the study will be free for the participants. We will disseminate the main results to all the participants in the form of an accessible newsletter. Patient advisors were not used in the conduct of this study.

### Intervention

The study intervention protocol was determined according to the classical principles of traditional Chinese medicine. All acupuncturists had at least 5 years of acupuncture experience. The participants will be asked not to take any other medications for pain or depression and, if they did, to document the pills and dosage. In addition, the HC participants will not receive any medical intervention, except blood and P300 tests at baseline.

### Real acupuncture treatment

Participants in the RA group will receive acupuncture at Baihui (DU20), Yintang (EX-HN3), Renzhong (DU27), Chenjiang (RN24), Hegu (LI4, bilateral), and Taichong (LR3, bilateral). After skin disinfection, sterile adhesive pads will be placed on the above points, and then needles (Hwato, Suzhou, China) will be inserted through the pad. At the DU20 and EX-HN3 points, needles will be obliquely inserted about 16 mm deep, and at the DU27, RN24, L14, and LR3 points, needles will be vertically inserted approximately 12 mm, 12 mm, 25 mm, and 25 mm deep, respectively. All these points will be stimulated manually until patients feel heaviness, soreness, distension, or numbness sensation (deqi), as reported in our previous study [15]. Each acupuncture session will be continued for 30 min and then the pads will be removed with a disinfection swab. The acupuncture treatment will be administered twice per week for a total of 16 sessions over a period of 8 weeks.

### Sham acupuncture treatment

Participants in the SA group will receive the same procedure as the RA group but using non-insertion sham acupuncture [19] (Fig. 3). Briefly, after skin disinfection, sterile adhesive pads will be placed on the same acupoints as the RA group. Then, blunt needles will be inserted into the sterile adhesive pads but they will not break the skin and they will cause a tickling, pricking feeling similar to real acupuncture.

**Fig. 3 Fig3:**
[figure not shown]
Illustration of the acupuncture needle structure

### Discontinuations

If participants are unable or unwilling to complete the treatment, we consider will them to be treatment dropouts. This could occur if participants withdraw consent to receive the study intervention or if the psychiatrist assessment suggests that it is inappropriate to continue the study intervention due to, for instance, depression or pain condition persists or getting worse, serious suicidal ideation, or a severe adverse event.

### Outcome measures

#### Primary outcomes

The primary outcomes are the changes in HAMD-17 and BPI scores from baseline to 12 weeks. HAMD-17 is a 17-item self-reported questionnaire; the higher the score is, the more severe the depression. A previous study showed that HAMD-17 has good validity and reliability for the assessment of depression severity. The BPI was first developed to measure pain in cancer patients, but it has become one of the most widely used pain measures, used for musculoskeletal pain and postsurgery pain [20, 21]. The BPI is a 15-item inventory that contains 2 dimensions: the intensity of the pain and interference with everyday activities. All the items are measured using a numerical rating scale from 0 to 10. The higher the score, the more severe the pain is.

#### Secondary outcomes

Secondary outcomes include the rates of depression response and remission at the 8th week (endpoint), where response is defined as a reduction of 50% of the HAMD-17 score and remission as a HAMD-17 score of 7 or less [22]; the rates of pain response at the 8th week, where response is defined as a reduction of 2 points of the BPI-WP [23, 24]; the Beijing version of Montreal Cognitive Assessment (MoCA); the World Health Organization Quality of Life BREF (WHOQOL-BREF); event-related potential (P300); and the serum level of BDNF and DNA methylation of BDNF. The Beijing version of the MoCA is highly recommended as a clinical and research tool for evaluating cognitive impairment. Previous studies proved that B-MoCA has a reliability of 0.73 Cronbach’s alpha in patients with obstructive sleep apnea-hypopnea syndrome with cognitive impairment [25]. The total MoCA score is 30 points, and less than 26 points is considered to indicate cognitive impairment. In addition, P300 will be used as an objective index to measure cognitive impairment, because it is based on the electrophysiological brain response. Previous studies have shown a decrease in amplitude and an increase in latency in depression patients [26]. The WHOQOL-BREF is an abbreviated version of the WHOQOL-100, which contains 26 items. In this trial, the official Chinese version of the WHOQOL-BREF, which has been approved by the WHOQOL Group [27], will be used to evaluate the changes in quality of life. BDNF is a biomarker for depression patients [14, 28]. All depression and CMSP participants will receive blood tests and P300 tests at baseline and 8 weeks. ELISA, RT-PCR, and BSP will be applied to measure the serum BDNA level and BDNF DNA methylation. The correlation between BDNF and symptoms will be determined.

### Incidence of adverse events

Acupuncturists will be asked to report and record any acupuncture-related adverse events (AEs), such as local bleeding, hematoma, fainting, local infection, unbearable prickling, or other discomfort after treatment. Severe AEs will be reported to the Research Ethics Committee within 24 h, which will provide medical advice to the research team, and the latter will evaluate whether the participant should continue the trial.

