## Methods

### Study design

This project is a randomized controlled clinical trial with 3 groups: real acupuncture (RA), sham acupuncture (SA), and healthy control (HC) at a ratio of 2:2:1. This trial was approved by the ethics committee of Guangdong Provincial Hospital of Chinese Medicine (Z2017-162-01). Before randomization, written informed consent will be obtained from all participants prior to their involvement. Primary and secondary outcome measures will be assessed at baseline, 4, 8, and 12 weeks. Outcome assessors and statisticians will be blinded in this study. An overview of the trial is shown in Fig. 1. This protocol was reported according to the Standard Protocol Items: Recommendation for Interventional Trials (SPIRIT) statement requirements. The complete SPIRIT checklist is available in Additional file 1 and Fig. 2.

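### Adverse events are recorded by acupuncturists who know the arm, and only as acupuncture-related events under the one rule stated, so AE rates by arm risk differential ascertainment

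*Protocol article*

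**What the plan says.** The Protocol article, section Incidence of adverse events, says who records and what: "Acupuncturists will be asked to report and record any acupuncture-related adverse events (AEs"). The examples given are "such as local bleeding, hematoma, fainting, local infection, unbearable prickling, or other discomfort after treatment". The next sentence deals with severity and does not repeat the relatedness restriction: "Severe AEs will be reported to the Research Ethics Committee within 24 h".

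On blinding, the section Blinding states: "The participants, outcome assessors, and statisticians will be blinded to treatment allocation". Acupuncturists are not in that list. The same section adds: "The acupuncturist will not provide any clues about the allocation information to the participants, assessors, or statisticians", which presupposes that they hold that information. The section Sham acupuncture treatment explains why they must: "blunt needles will be inserted into the sterile adhesive pads but they will not break the skin".

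The section Discontinuations gives, as examples of why a psychiatrist assessment may end treatment, "depression or pain condition persists or getting worse, serious suicidal ideation, or a severe adverse event".

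**The concern.** Two things are settled at the moment of collection that are better kept apart: whether an event occurred, and whether the needling caused it. Under the stated rule the second question filters the first, and the person answering it knows whether the skin was pierced. For a haematoma that hardly matters. For fainting, a pain flare or general discomfort, the causal judgement may come more readily in one arm than in the other. A comparison of recorded AEs between real acupuncture (RA) and sham acupuncture (SA) would then mix true harm with differing readiness to attribute it. This cannot be repaired at analysis, because an event that was never written down cannot be tabulated.

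The second issue is one of scope. Worsening depression or pain and serious suicidal ideation are foreseen as reasons to stop, and they are listed alongside a severe adverse event rather than as instances of one. The AE section does not say whether they are logged as AEs or go into the 24-hour report. In a depressed population these are events that a safety table should treat unambiguously.

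**Working it through.** **Reading the sections side by side**

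| Question | Answer in the document | Section |
|---|---|---|
| Who records AEs? | The acupuncturists; no other recorder is named | Incidence of adverse events |
| Which events? | Those related to acupuncture, with procedural examples plus an open category of discomfort after treatment | Incidence of adverse events |
| Does the recorder know the arm? | Yes: not listed as blinded, told not to reveal the allocation, and uses a blunt non-penetrating needle in SA | Blinding; Sham acupuncture treatment |
| Who is blinded and sees patients on a schedule? | Outcome assessors, at weeks 4, 8 and 12 after baseline | Blinding; Study design |
| Do the assessors have an AE role? | None stated | Incidence of adverse events |
| Are worsening and suicidal ideation AEs? | Not stated; listed next to a severe AE as grounds for stopping | Discontinuations |
| Is an RA versus SA test of AEs planned? | None stated | Statistical analysis of the trial outcomes |

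It follows that relatedness is judged at collection and with knowledge of the arm.

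**How much could it matter?** The document gives no AE rate and no AE test, so there is no figure to reproduce. What follows is an illustration on assumed rates.

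Inputs: n = 24 per arm (section Sample size calculation). Assumed: the same true incidence p in both arms, from 10% to 40%, and recording probabilities r_RA and r_SA.

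Formulas: recorded rate = p × r; expected recorded count = 24 × p × r; recorded risk ratio = r_RA / r_SA, because p cancels.

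| Recording RA / SA | Risk ratio (truth 1.0) | Expected counts, p = 10% | Expected counts, p = 40% |
|---|---|---|---|
| equal | 1.00 | equal | equal |
| 90% / 70% | 1.29 | 2.2 vs 1.7 | 8.6 vs 6.7 |
| 90% / 50% | 1.80 | 2.2 vs 1.2 | 8.6 vs 4.8 |
| 50% / 90% | 0.56 | 1.2 vs 2.2 | 4.8 vs 8.6 |

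Worked line: p = 30% with 90% / 50% gives 24 × 0.30 × 0.90 = 6.5 against 24 × 0.30 × 0.50 = 3.6, and 0.27 / 0.15 = 1.80.

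Chance of a nominal two-sided p < 0.05 in the direction of the distortion, by normal approximation: Φ[(d − 1.96 × se0) / se1], where d is the difference in recorded rates, se0 the pooled and se1 the unpooled standard error. For the worked line:

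- d = 0.27 − 0.15 = 0.12; pooled rate = 0.21
- se0 = √(0.21 × 0.79 × 2/24) = 0.118
- se1 = √[(0.27 × 0.73 + 0.15 × 0.85)/24] = 0.116
- Φ(−0.95) = 0.17

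For 90% / 50% the result runs from about 8% (p = 10%) to 23% (p = 40%). For 90% / 70% it runs from about 4% to 9%. With counts this small the approximation is rough. In a trial of this size, the main effect of differential recording would be on the estimate rather than on a significance test.

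**The case against.** The strongest reply is that this is a journal article. It says what acupuncturists are asked to record, not that nobody else records anything; all-cause collection and relatedness procedures may sit in the full protocol. That stands as far as it goes. A reader might infer that events not attributed to needling are never recorded, but the text does not exclude other recorders. The point rests on the rule that is stated, not on what is absent.

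A reader might also infer that the RA versus SA safety comparison is biased, probably against RA. The document does not support that. It states no such comparison, and the direction depends wholly on assumed recording rates. Fainting and discomfort after treatment are also named as recordable without distinction by arm, which narrows the acupuncturist's discretion. A risk is all that can be claimed.

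The third tempting reading is that worsening depression or suicidality escapes the safety record. That goes too far. The psychiatrist route identifies such patients. The Hamilton Depression Rating Scale and the Brief Pain Inventory are primary outcomes with blinded assessors, and "Primary and secondary outcome measures will be assessed at baseline, 4, 8, and 12 weeks". The severe-AE sentence does not repeat the relatedness limit.

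These safeguards are partial, though. A stopping route is not a count of events by arm. The scales are analysed as repeated measures, not as incidence of worsening. Because missing values are replaced by the latest assessment, a patient who stops for worsening between visits and does not return contributes the score from before the deterioration.

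**Conclusion.** The point holds as a risk of differential ascertainment, not as a demonstrated bias. The one AE collection rule stated puts an unblinded relatedness judgement ahead of recording, and any AE incidence reported by arm inherits it. Neither size nor direction can be derived from the document. Under the assumptions above the recorded risk ratio ranges from 0.56 to 1.80 when the truth is 1.0, and equal recording in both arms removes the distortion altogether. Those figures show only what is possible with 24 per arm.

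The sections Discontinuations and Incidence of adverse events also leave open whether worsening and serious suicidal ideation are logged and reported as AEs, and they need to be reconciled. This is a cheap improvement; it does not threaten the primary analysis.

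**What to change.** - Record all adverse events in the RA and SA arms, whatever the presumed cause.
- Have the blinded outcome assessors ask every patient the same open AE question at the existing 4, 8 and 12 week visits. The week 12 visit also covers the time after the 8-week treatment period.
- Keep the acupuncturist's log for local needle reactions, which only the operator may see.
- Judge relatedness as a separate step after recording, blind to arm where possible.
- Tabulate all-cause AEs by arm.
- State whether the events named under Discontinuations enter the AE record and the 24-hour report, so that the two sections agree. If worsening is logged as an AE, show it on its own line, since depression and pain severity are also the primary outcomes.

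The cost is one case report form page and one question, asked by assessors already in place at visits already planned. The downside is a longer AE listing that includes unrelated events.
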